## 11.1 Centre responsibilities

All SAEs and reactions must be reported by the Principal Investigator at the participating centre to the WCTU unless the SAE/SAR is specified as not requiring immediate reporting (see below). All other AEs should be reported on either the treatment or follow-up CRFs as usual. The PI, or another appropriately qualified clinician registered on the delegation log, should assess the SAE to determine whether it is a reaction to protocol treatment (graded as definite, probable, possible or not related) and whether it is unexpected or expected in view of the SPCs or IB. A completed SAE form for all events requiring immediate reporting should be faxed to the WCTU within 24 hours of knowledge of the event.

**SAE [contact]**

In addition to the standard SAE definition for the purposes of this protocol certain cetuximab hypersensitivity reactions (section 8.4.2) should be reported as SAEs.

The following events **do not** require reporting as SAEs:

- Disease progression or death as a result of disease progression
- Hospitalisation as a result of disease progression (for example, procedures involving the insertion of a PEG or stent as these are procedures for routine management)
- Hospitalisation as a result of expected adverse events related to anti-cancer therapy (for example neutropenic sepsis)

However, these should be completed on the relevant CRF and forwarded to WCTU in the usual timeframes for CRF pages.

Serious adverse events should continue to be reported whilst the participant is on-trial (up to the 96 week visit) and until 30 days after the patient receives their last on-trial dose of the investigational medicinal product. Serious adverse reactions must continue to be reported until the end of follow up (up to 5 years).

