| 
Grade 2
Rash; flushing; urticaria;
dyspnoea; drug fever ≥ 38°C
                                                                                                   | 
Stop cetuximab infusion.
Administer bronchodilators, oxygen etc. as medically indicated.
Resume infusion at 50% of previous rate once allergic/hypersensitivity reaction has resolved or decreased to grade 1 in severity, and monitor closely for any worsening.
Cetuximab infusion time can be increased to a maximum of 4 hours; the infusion time will remain prolonged for subsequent infusions.
 
If patient has a second reaction on this prolonged infusion rate, the infusion should be stopped and not reintroduced.
This second reaction must be reported as a serious adverse event.
 |
| 
Grade 3: Symptomatic
bronchospasm, with or without
urticaria; parenteral
medication(s) indicated;
allergy-related
oedema/angioedema;
hypotension
 | 
Stop cetuximab infusion immediately and do not reintroduce.
 
Administer adrenaline, bronchodilators, antihistamines, glucocorticoids, intravenous fluids, vasopressor agents, oxygen etc., as medically indicated.
 
This must be reported as a serious adverse event.
                                                                                                                                                                                                                                                                                                                                     |
| 
Grade 4: Anaphylaxis
                                                                                                                                                     | 
Patients have to be withdrawn immediately from treatment and must not receive any further cetuximab treatment.
 
This must be reported as a serious adverse event.
                                                                                                                                                                                                                                                                                                                                                                                                                                               |

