## 11. SAFETY REPORTING

The Medicines for Human Use (Clinical Trials) Regulations 2004 apply for this protocol:

**Adverse Event (AE):** any untoward medical occurrence in a subject to whom a medicinal product has been administered, including occurrences which are not necessarily caused by or related to that product.

**Adverse Reaction (AR):** any untoward and unintended response in a subject to an investigational medicinal product which is related to any dose administered to that subject.

**Serious Adverse Event (SAE):** Any adverse event that

- ◆ results in death
- ◆ is life-threatening\*
- ◆ requires hospitalisation or prolongation of existing hospitalisation\*\*
- ◆ results in persistent or significant disability or incapacity
- ◆ is a congenital anomaly or birth defect
- ◆ Other important medical events\*\*\*

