|                                                                   | Hand foot syndrome                | Injection site reaction   | Subacute intestinal obstruction |
|                                                                   | Hypocalcaemia                     | Leukocytes                | Weight loss                     |
|                                                                   | Hypercalcaemia                    | Nephrotoxicity            |                                 |
|                                                                   | Infection with normal ANC         | Neutrophils (ANC)         |                                 |
|                                                                   | Injection site reaction           | Neuropathy – motor        |                                 |
|                                                                   | Leukocytes                        | Neuropathy – sensory      |                                 |
|                                                                   | Myelosuppression                  | Nausea                    |                                 |
|                                                                   | Nail changes                      | Oesphagitis               |                                 |
|                                                                   | Nausea                            | Ototoxicity               |                                 |
|                                                                   | Neutrophils (ANC)                 | Platelets                 |                                 |
|                                                                   | Oesphagitis                       | Tinnitus                  |                                 |
|                                                                   | Platelets                         | Thrombosis/Thrombus       |                                 |
|                                                                   | Stomatitis                        |                           |                                 |

For all adverse reactions:

- Grade 1-2: Reported only on CRF Toxicity form
- Grade 3-5\*: Reported on CRF Toxicity form and on SAE form as SAR (\*where Grade 5 is death)

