## **11.3 WCTU responsibilities**

Following the initial report of an SAE, further follow up information may be requested by the WCTU. The patient will be identified by trial number, date of birth and initials only. The patient's name should not be used on any correspondence.

Velindre Hospital NHS Trust is undertaking the duties of trial sponsor and has delegated to the WCTU the responsibility for the reporting of SUSARs and other SARs to the regulatory authorities (MHRA and the relevant Ethics Committees) as follows:

- SUSARs which are fatal or life-threatening must be reported not later than 7 days after the sponsor is first aware of the reaction. Any additional relevant information must be reported within a further 8 days.
- SUSARs that are not fatal or life-threatening must be reported within 15 days of the sponsor first becoming aware of the reaction.
- A list of all SARs (expected and unexpected) will be reported annually to the MHRA and MREC and a copy sent to all the PIs.

Once an SAE is received at the WCTU, it will be evaluated by staff at the WCTU and the Chief Investigator (or their delegate) for seriousness, expectedness and causality. Investigator reports of suspected SARs will be reviewed immediately and those that are SUSARs identified and reported to the MHRA, MREC and Merck KGaA.

The causality and expectedness assessment given by the PI cannot be overruled by the CI (or their delegate) and in the case of disagreement, both opinions will be provided with the report. SAEs will be handled at the highest level of event categorisation. This

ensures that all SAEs which are assessed as SARs or SUSARs (by either the CI or PI at any stage) will be reported correctly and included into annual and investigator safety reports.

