## **12.5 Statistical analyses**

All analyses will be on an intention-to-treat basis, i.e. all patients randomised will be included, and all patients will be analysed according to their allocated group whatever treatment they received.

A detailed statistical analysis plan will be prepared and finalised before analysis of the data.

The main analysis will compare overall survival between the two groups using a logrank test.

The secondary outcomes of proportions of patients with SAEs will be compared using a chi-squared test.

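### The protocol's rules on which events are reported as SAEs conflict, so the SAE proportion compared in section 12.5 depends on the rule a site follows

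*Protocol*

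**What the plan says.** Five places in the protocol bear on what is reported as an SAE.

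- **Section 11, definition.** An adverse event is serious if, among other criteria, it "requires hospitalisation or prolongation of existing hospitalisation". The comment on this criterion counts any inpatient stay, even a precautionary one.
- **Section 11, below the table of expected side effects.** For all adverse reactions, grades 1-2 are "Reported only on CRF Toxicity form". Grades 3-5 are "Reported on CRF Toxicity form and on SAE form as SAR". Neither line makes an exception for expected events or for admission.
- **Section 11.1, opening.** Sites report all SAEs and reactions "unless the SAE/SAR is specified as not requiring immediate reporting (see below".
- **Section 11.1, list of events that do not require reporting as SAEs.** It includes "Hospitalisation as a result of expected adverse events related to anti-cancer therapy (for example neutropenic sepsis". These events are to be entered on the relevant CRF and returned in the usual time.
- **Section 8.4.2, on a repeat grade 2 cetuximab hypersensitivity reaction.** "This second reaction must be reported as a serious adverse event". Section 11.1 confirms that such reactions are added to the standard definition.

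Two further places use the result. Section 12.5: "The secondary outcomes of proportions of patients with SAEs will be compared using a chi-squared test". Section 11.3: "A list of all SARs (expected and unexpected) will be reported annually to the MHRA and MREC".

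**The concern.** An outcome variable has to mean the same thing at every site and in both arms. Here sites can each comply with the protocol and still produce different SAE counts for identical patients. Section 12.5 states no other between-arm toxicity test, so the one it does state has no fixed numerator.

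Three things are at stake. The comparison may leave out expected toxicity that leads to admission, which is where much of any harm added by cetuximab could fall. The SAE monitoring by the Chief Investigator and trial management group, which section 12.2 calls real-time, would not receive waived admissions through the 24-hour route. And the documents do not show how waived events get into the annual list of serious adverse reactions (SARs). Section 11 requires seriousness, causality and expectedness on the SAE form, but for the toxicity CRF it mentions only grades.

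**Working it through.** **Step 1. One case under each rule.** Take diarrhoea. The section 11 table lists it as expected (capecitabine and radiotherapy), and Appendix XI includes hospitalisation in its grade 3 criteria. A patient admitted with grade 3 treatment-related diarrhoea is handled as follows:

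| Rule | Result |
|---|---|
| Section 11, definition | SAE, because admitted |
| Section 11, grading rule | SAE form, because grade 3 |
| Section 11.1, list | Not required as an SAE; CRF only |
| Section 11.1, opening | SAE, exempt only from immediate reporting |

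The same holds for any expected grade 3-4 reaction that leads to admission.

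**Step 2. Neighbouring cases.** Read literally, a grade 2 reaction with a precautionary admission is an SAE by the definition but goes only on the CRF by the grading rule. A grade 3 reaction managed without admission need not meet any seriousness criterion, yet the grading rule puts it on the SAE form. The conflict can therefore push the count up as well as down.

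**Step 3. Comparability of the arms.** Only research-arm patients can have a repeat grade 2 cetuximab reaction. Section 8.3.2 puts hypersensitivity at about 5%, about half of it severe. The non-severe part is 210 x 0.05 x 0.5 = about 5 patients, and a second reaction is still needed, so few such events are likely. A smaller effect runs the other way: the table lists dyspnoea, for example, under cetuximab only. An admission for it could be exempt as expected in the research arm and reportable in the control arm.

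**Step 4. Size.** The protocol states no SAE rate, effect or power for this test. The only design figure available is 210 per arm from the survival calculation, which reproduces: HR = ln(0.475)/ln(0.35) = 0.709; 266 events (Schoenfeld) or 271 (Freedman) against 269 stated; about 418 patients against 420.

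For illustration only, take the one randomised cetuximab toxicity contrast in the protocol (section 2.4, head and neck cancer): grade 3-4 skin reactions of 18% v 34%. Let an assumed share s, equal in both arms, reach the SAE count, so that p1 = 0.18s and p2 = 0.34s. With n = 210 per arm, two-sided 5% and p the mean of p1 and p2:

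power = Φ{[(p2 − p1) − 1.96·√(2p(1 − p)/n)] / √([p1(1 − p1) + p2(1 − p2)]/n)}

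For s = 1: (0.16 − 1.96 x 0.0428)/0.0421 = 1.81, giving 96.5%.

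| Share counted (assumed) | Rates compared | Power |
|---|---|---|
| 100% | 18.0% v 34.0% | 96.5% |
| 75% | 13.5% v 25.5% | 87.6% |
| 50% | 9.0% v 17.0% | 68.5% |
| 25% | 4.5% v 8.5% | 38.3% |
| 10% | 1.8% v 3.4% | 17.6% |

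The first row corresponds to the grading rule being followed everywhere. The table shows how power responds to the share counted. It says nothing about what that share would be: the contrast comes from another disease, and many skin reactions would not involve admission and so would fall outside the exemption.

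**The case against.** The strongest reply is that section 11.1 opens by calling the carve-out a matter of timing, that waived events still go on the CRF, and that the SAE flowchart, a figure not available for this review, may settle the routing. It stands that the events are recorded under every reading. It does not remove the conflict: the list says these events do not require reporting as SAEs, the grading rule allows no exception, and a flowchart would leave both texts in place.

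A second reply is that toxicity as an outcome is CTCAE- and RTOG-graded (section 12.2), that section 12.5 leaves detail to a statistical analysis plan, and that section 14 also compares quality of life between arms, including dyspnoea, rash and diarrhoea. This is fair. The lack of a grade-based test in the protocol is not a fault by itself. But an analysis plan cannot make the SAE count consistent once sites have reported by different rules, unless seriousness was recorded for the waived events.

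A reader might go further and infer that the test would miss most of the harm from cetuximab, or lose a definite amount of power. The documents do not support either. Under the grading rule no grade 3-5 reaction is lost. On the literal reading of the list, the treatment-toxicity exemption covers admissions for expected events; fatal, life-threatening and disabling events still meet other SAE criteria. No admission rate or exempt share is given.

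Nor does it follow that an excess of mucositis would go unseen. Section 12.4 plans a toxicity analysis after 60 patients that names mucositis, then annual reviews by the data monitoring committee, which also reviews toxicity before Stage 2 (section 12.3). CRFs are due within 4 weeks of the visit (section 10.2). The annual SAR list is not contradicted either, since the trials unit holds the CRFs; the gap is that no route into the list is shown.

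**Conclusion.** The concern holds as an inconsistency with a consequence for a stated analysis. Sections 11 and 11.1 give incompatible instructions for expected grade 3-4 reactions that lead to admission, and the SAE proportion tested in section 12.5 inherits the ambiguity. That conclusion rests on the text alone.

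The size is unknown. The share of expected toxicity left out of the count runs from none, if every site follows the grading rule, to admissions for expected toxicity that meet no other seriousness criterion, if every site follows the list. The power figures depend wholly on an assumed share and a borrowed contrast. The imbalance from repeat grade 2 reactions is real but small, a few patients at most on the protocol's own 5% figure.

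This should be fixed. It affects a secondary outcome and the completeness of real-time SAE monitoring, not the survival comparison.

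**What to change.** 1. Reconcile the section 11 definition, the grading rule, and both parts of section 11.1 to one SAE definition applied in both arms.
2. Limit the exemption for expected treatment-related admissions to the timing of reporting, as the opening of section 11.1 words it.
3. Add to the toxicity CRF a field for whether the event was serious and by which criterion, so that waived events still enter the SAE count and the annual SAR list in section 11.3.
4. In section 12.5, count patients with at least one event meeting the section 11 definition, whatever its expectedness or reporting route. Specially designated cetuximab reactions would still be reported, but would enter this count only if they meet that definition.
5. Alongside it, compare the proportion of patients whose worst CTCAE grade is 3 or above, taken from the CRF. This does not depend on SAE routing.

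The cost is protocol wording, one CRF field, slightly more recording at sites and one extra table. No more patients are needed.

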## **11.2 Reporting pregnancies whilst participating in SCOPE 1**

Patients who are pregnant are excluded from participating in the SCOPE 1 clinical trial. The reason for this being risks involved if a foetus is exposed to chemotherapy and radiotherapy. However, it is important to consider the potential for foetal exposure to these agents (resulting from maternal or paternal exposure) and have suitable procedures in place if this should arise. Pregnancy, or the pregnancy of a partner, occurring whilst participating in the SCOPE 1 trial, although not considered an SAE, must be notified to the WCTU within the same timelines as an SAE. In the event of a pregnancy in a trial participant, or the partner of a trial participant, the WCTU must be contacted immediately to request a Pregnancy Report Form. The outcome of a pregnancy should be followed up carefully and any abnormal outcome of the mother or the foetus should be reported. This also applies to pregnancies following the administration of the investigational product to the father prior to sexual intercourse.

## **11.3 WCTU responsibilities**

Following the initial report of an SAE, further follow up information may be requested by the WCTU. The patient will be identified by trial number, date of birth and initials only. The patient's name should not be used on any correspondence.

Velindre Hospital NHS Trust is undertaking the duties of trial sponsor and has delegated to the WCTU the responsibility for the reporting of SUSARs and other SARs to the regulatory authorities (MHRA and the relevant Ethics Committees) as follows:

- SUSARs which are fatal or life-threatening must be reported not later than 7 days after the sponsor is first aware of the reaction. Any additional relevant information must be reported within a further 8 days.
- SUSARs that are not fatal or life-threatening must be reported within 15 days of the sponsor first becoming aware of the reaction.
- A list of all SARs (expected and unexpected) will be reported annually to the MHRA and MREC and a copy sent to all the PIs.

Once an SAE is received at the WCTU, it will be evaluated by staff at the WCTU and the Chief Investigator (or their delegate) for seriousness, expectedness and causality. Investigator reports of suspected SARs will be reviewed immediately and those that are SUSARs identified and reported to the MHRA, MREC and Merck KGaA.

The causality and expectedness assessment given by the PI cannot be overruled by the CI (or their delegate) and in the case of disagreement, both opinions will be provided with the report. SAEs will be handled at the highest level of event categorisation. This

ensures that all SAEs which are assessed as SARs or SUSARs (by either the CI or PI at any stage) will be reported correctly and included into annual and investigator safety reports.

### Flowchart for SAEs

[figure not shown]

**CRF:** Case Report Form  
**IB:** Investigator Brochure  
**SAE:** Serious Adverse Event  
**SAR:** Serious Adverse Reaction  
**SPC:** Summary of Product Characteristics  
**SUSAR:** Suspected Unexpected Serious Adverse Reaction

## 12. STATISTICAL CONSIDERATIONS

### 12.1 Method of randomisation

Patients will be randomised centrally using the method of minimisation which includes a random element. Patients will be stratified for a number of clinically important stratification factors. The randomisation ratio for control:research arm will be 1:1.

The trial will be conducted in two stages.

### 12.2 Outcome measures

#### Stage 1:

The primary outcome measure is treatment failure rate in the research arm. Treatment failure rate will be assessed at 24 weeks (12 weeks after completion of CRT) and is defined as pathologically confirmed (by endoscopic assessment and/or biopsy) residual disease and/or CT scan of thorax and abdomen showing progressive disease according to RECIST criteria.

The secondary outcome measures are: toxicity and feasibility.

- **Toxicity:** will be scored using the NCI CTCAE v3.0 and RTOG acute radiation morbidity scoring criteria (Appendix XII) at baseline, during treatment and at pre-specified time points on follow-up. Serious adverse events will be monitored “real-time” by the Chief Investigator and TMG.
- **Feasibility:** will be measured through the number of protocol dose modifications and delays.

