## **Follow up**

- Patients will be seen for clinical surveillance and toxicity assessments three monthly for the first year, four monthly for the second year and yearly for a minimum of five years after treatment, after which follow up should be according to local guidelines.
- Endoscopy and/or CT scan to investigate symptoms suspicious of recurrence as clinically indicated.
- Quality of Life and Health Economics questionnaires annually.

**Primary outcome of stage 1:** Treatment failure rate in the research arm. This will be assessed at 24 weeks (12 weeks after completion of CRT) and is defined as residual disease pathologically confirmed by endoscopic assessment, biopsy and CT scan of thorax and abdomen. The secondary outcome measures are toxicity and feasibility.

**Primary outcome of stage 2:** Overall survival calculated from the date of randomisation to death from any cause. The secondary outcome measures are toxicity, quality of life, quality assurance of radiotherapy and health economics.

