### 12.3 Sample size calculation

#### Stage 1:

The treatment failure-free rate in patients treated with CRT is approximately 60% at 24 weeks. With the addition of cetuximab it is felt that a treatment failure-free rate of less than 60% would not be sufficiently large enough to warrant further investigation in a Phase III setting, but that a rate of 75% or higher would warrant further investigation. Using a Fleming's single stage design,  $p_1=0.60$  and  $p_2=0.75$ , setting  $\alpha=0.05$  and 90% power 83 patients would be required. To allow for 10% not being assessable and with a 1:1 allocation 90 patients will be recruited into each arm, a total of 180 patients. The IDMC will review the treatment failure-free rate, along with toxicity and feasibility, before they endorse continuation into Stage 2.

#### Stage 2

Calculations were performed using the ART package in Stata 9 assuming a 3 year recruitment period followed by 1 year of follow up (based on a 2-sided log rank test). The 2 year overall survival rate in patients treated with CRT is approximately 35%. In order to detect an improvement in 2 year overall survival from 35% to 47.5% (Hazard Ratio [HR] =0.71) with 80% power at a 5% significance level a total of 420 patients (269 events) are required. A total of 210 patients will be recruited to each arm.

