### **Reporting of results**

All patients included in the study must be assessed for response to treatment, even if there are major protocol treatment deviations or if they are ineligible. Each patient will be assigned one of the following categories: 1) complete response, 2) partial response, 3) stable disease, 4) progressive disease, 5) early death from malignant disease, 6) early death from toxicity, 7) early death because of other cause, or 9) unknown (not assessable, insufficient data).

All of the patients who met the eligibility criteria should be included in the main analysis of the response rate. Patients in response categories 4-9 should be considered as failing to respond to treatment (disease progression). Thus, an incorrect treatment schedule or drug administration does not result in exclusion from the analysis of the response rate. Precise definitions for categories 4-9 will be protocol specific.

All conclusions should be based on all eligible patients.

Sub analyses may then be performed on the basis of a subset of patients, excluding those for whom major protocol deviations have been identified (e.g., early death due to other reasons, early discontinuation of treatment, major protocol violations, etc.). However, these sub analyses may not serve as the basis for drawing conclusions concerning treatment efficacy, and the reasons for excluding patients from the analysis should be clearly reported.

The 95% confidence intervals should be provided.

**From:** <http://ctep.cancer.gov/forms/quickrcst.doc>

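### The Stage 1 activity endpoint has two definitions, neither counts early death as failure, and the test is sized on assessable patients although all analyses are to include everyone randomised

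*Protocol*

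**What the plan says.** Section 12.2 (Stage 1) names the treatment failure rate in the research arm as the primary outcome, assessed at 24 weeks, with failure defined as "pathologically confirmed (by endoscopic assessment and/or biopsy) residual disease and/or CT scan of thorax and abdomen showing progressive disease according to RECIST criteria". Either limb is enough.

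The Trial Synopsis defines the same outcome as "residual disease pathologically confirmed by endoscopic assessment, biopsy and CT scan of thorax and abdomen". It joins the three investigations with *and* and has no RECIST-progression limb.

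Section 12.3 (Stage 1) sets the design rates: "a treatment failure-free rate of less than 60% would not be sufficiently large enough", whereas "a rate of 75% or higher would warrant further investigation". A Fleming single-stage design with alpha 0.05 and 90% power gives 83 patients. Then: "To allow for 10% not being assessable and with a 1:1 allocation 90 patients will be recruited into each arm". No pass mark is printed.

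Section 12.5 applies intention to treat to all analyses: "all patients randomised will be included, and all patients will be analysed according to their allocated group". It does not say how a patient without a week-24 assessment is classified.

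Appendix XIII, under its heading on reporting of results, lists early death and not assessable among its response categories and says: "Patients in response categories 4-9 should be considered as failing to respond to treatment". It leaves the precise definitions of those categories to the protocol, and section 12 supplies none.

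**The concern.** A patient who dies in week 15, or is too ill for endoscopy and CT at week 24, meets neither limb of section 12.2. The plan leaves three possible treatments of that patient: excluded as not assessable (the reading that the 10% allowance suggests), counted as failure-free because no failure was documented, or counted as failed (the line that Appendix XIII takes for response rate). The two definitions also disagree about a patient with negative biopsies and new distant lesions on CT, who is a failure under section 12.2 but, read literally, not under the synopsis.

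These choices matter because Stage 1 is a single-arm test against fixed rates. Section 12.2 notes that activity is not formally assessed in the control arm, so no concurrent comparison absorbs a bias in the rate. The result informs whether 240 more patients are randomised. Leaving out deaths and unassessable patients would raise the apparent failure-free rate most when the regimen is toxic or inactive.

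**Working it through.** **Inputs.** From section 12.3: p1 = 0.60, p2 = 0.75, alpha = 0.05, power 90%, 83 required, 10% not assessable, 90 recruited per arm, and 2-year survival of 35% and 47.5% from the Stage 2 calculation.

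**1. The plan's own figure.** n = [(z(1−α)·√(p1(1−p1)) + z(power)·√(p2(1−p2))) / (p2−p1)]².
- One-sided: [(1.645 × 0.4899 + 1.2816 × 0.4330) / 0.15]² = 82.3, so 83. This matches.
- Two-sided: 102.0, so 103. This does not match.

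The stated 83 is therefore a one-sided calculation in assessable patients. A 10% loss from 90 leaves 81. Keeping 83 would need 83/0.9 = 92.2, so 93; 90 covers a loss of 7.8%.

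**2. Effect of exclusion.** Assume that the true failure-free rate over all 90 is 60%, that a share m dies or is unassessed, and that all of these are true failures who leave the denominator. The apparent rate is 0.60/(1−m). The pass mark is the smallest count with exact one-sided alpha of at most 5% at 60%.

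| m | Apparent rate | Pass mark | Chance of passing |
|---|---|---|---|
| 0% | 60.0% | 63/90 | 3.2% |
| 5% | 63.2% | 60/86 | 12.2% |
| 10% | 66.7% | 57/81 | 28.1% |
| 15% | 70.6% | 54/76 | 52.2% |
| 20% | 75.0% | 51/72 | 83.0% |

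Letting the number excluded vary binomially gives 12.3% at m = 5% and 30.6% at m = 10%.

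If such patients were instead counted as failure-free among 90, the chance of passing at 63/90 would be 18.9% and 55.2% at m = 5% and 10%.

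**3. How large m might be.** The protocol gives no mortality figure for week 24. Under an assumed constant hazard, deaths by week 24 are 1 − S^(24/104.36): 21.4% for S = 0.35 and 15.7% for S = 0.475. The chance of passing would then be about 90% and 57%. These values are illustrative only.

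**4. The other reading of the benchmark.** If 60% is a rate among assessed patients, excluding the unassessed leaves the exact false-pass rate at 3.5% (57/81) or 4.1% (58/83), within the intended 5%.

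**5. After the fix.**
- All 90 analysed, with 60% and 75% as all-patient rates: pass at 63 or more, exact one-sided alpha 3.2%, power 88.7%.
- If 75% is a rate among assessed patients, the all-patient rate is 0.75 × 0.95 = 71.25% at 5% loss and 0.75 × 0.90 = 67.5% at 10% loss. Power at 63/90 falls to 65% and 35%.
- If both rates are restated for 10% loss (0.60 × 0.90 = 54% and 67.5%), the exact rule is 57/90, with alpha 4.7% and power 83%.

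**The case against.** The strongest reply is that exclusion is inferred. Section 12.3 gives a recruitment allowance, not an analysis rule; section 12.5 points to all randomised patients; and a detailed analysis plan is promised, where handling of missing assessments is often placed. It stands that no sentence says deaths are dropped. But what counts as failure and who is in the denominator define the primary outcome. The protocol chose to fix both and did so inconsistently.

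The second reply is about the benchmark. Section 2.4 reports endoscopy-negative rates with a mean of 61%, which may describe only patients who had an endoscopy. Part or all of the excess would then cancel. This stands, and the documents do not settle it.

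Third, the early-death figures are soft. Entry requires performance status 0–1, non-metastatic disease and fitness for all protocol treatment, and the UK series in section 2.2 had 2-year survival of 51% with no treatment-related deaths. This stands against relying on 16–21%, but not against 5% or the protocol's own 10%.

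Fourth, the IDMC also reviews toxicity and feasibility, and serious adverse events are monitored in real time, so heavy early mortality would be seen. That mitigates the risk. The activity criterion is nevertheless the only part of the Stage 1 decision with stated error rates.

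Appendix XIII cannot be used to close the gap. It is generic text on RECIST response rate, and section 12.2 calls on RECIST only for CT progression.

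**Conclusion.** The point holds in a conditional form. The two definitions differ, neither classifies death before week 24 as failure, and sizing on assessable patients conflicts with the all-randomised rule. A regimen at the 60% no-interest rate passes about 12% of the time at 5% loss and about 28% at 10%, against at most 5% intended, provided that three things are true: such patients are excluded, they are true failures, and 60% is an all-patient rate. If non-assessment were unrelated to outcome there would be no bias.

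A reader might infer that the 5% error rate is certainly lost, or that a false pass is more likely than not. The documents do not support either. The first depends on which patients the benchmark describes. The second needs early losses of roughly 15% or more, which rest on an assumed constant hazard. Nor is the final efficacy claim at risk: Stage 2 compares overall survival from randomisation to death from any cause. The harm is a wrong decision to continue to Stage 2.

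**What to change.** - Put one definition in the synopsis and section 12.2: failure is biopsy-confirmed residual disease, or RECIST progression at or before the week-24 assessment, or death from any cause before it.
- Make the primary Stage 1 analysis include all 90 research-arm patients, with a missing week-24 assessment counted as failure. Report the assessable-only rate as a sensitivity analysis.
- Confirm that 60% and 75% are all-patient rates, or restate both on that basis.
- Print the cut-off and label alpha as one-sided. With 60% and 75% as all-patient rates, the rule is at least 63/90.

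Cost: protocol wording and no new data, but a less favourable observed rate and possibly a lower stated power. With 60% and 75% confirmed, power is 88.7% at 90 patients; 91 patients with the same mark of 63 would give alpha 4.4% and power 91.6%. If the rates describe assessed patients, keeping 63/90 unchanged would stop an active regimen too often, so the cut-off, the stated power and possibly the sample size must be recalculated.
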